### Outcomes

#### Primary outcomes

The change in the MAGE before and after the intervention was chosen as the primary outcome for several reasons. First, MAGE is highly correlated with 24-h urinary 8-isoprostane F2α levels, an indicator of oxidative stress in the body, and increased levels of oxidative stress are in turn significantly and positively correlated with HbA1c in patients with type 2 diabetes (30). Second, MAGE is increased with the progression of atherosclerosis in patients with type 2 diabetes combined with atherosclerosis compared to that in those without atherosclerosis (5). The MAGE data calculated by the CGM assay are more accurate and of some reference value. Other indicators of GV, such as the TIR, area under the curve (AUC), variable coefficient (CV), and mean of daily differences (MODD), are also included in the primary outcomes.

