#### Secondary outcomes

Secondary outcomes consist of various metabolic and behavioral indicators, including changes in insulin, C-peptide, fasting blood glucose (FBG), HOMA-IR, HOMA-β, subjective appetite, satiety, hunger evaluated by the VAS, body height, and weight measurements.

We will assess changes in these outcomes in two different experimental periods: [1] from baseline to the end of the first intervention period (D3-D6) and [2] from the end of the run-in period to the end of the second intervention period (D10-D13). The acceptability and maintainability of the intervention will also be assessed after the completion of the interventions (D14).

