#### Continuous glucose monitoring

A 2-week CGM system (FreeStyle Libre Flash Glucose Monitoring System, Abbott) will be initiated on the test day at V1. The CGM will be attached to the hypogastrium on the test day morning. Subjects will be asked to measure their blood glucose levels using a glucometer (glucometer 550, Yuwell) four times a day (before breakfast, lunch, dinner, and bedtime) during the CGM measurement period to calibrate the instruments. The CGM will monitor dynamic blood glucose within the next 15 days. To exclude the potential impact of confounders, the data of dynamic blood glucose from D1, D3, D10, and D14 will be excluded in the final analysis, while data from D2 and D9 will be used as baseline values of two intervention periods. We will only use the data from the latter 3 days of each period rigorously and conservatively to maximally control the potential data contamination.

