### Comparisons

First, the three intervention arms will be combined as a group and compared with the control group to evaluate whether the premeal intervention could improve GV. Second, the two arms with high-protein snacks will be combined as a group and compared with the control group; moreover, the high-fat snack arm will be compared with the control group to evaluate whether the two snacks (high-protein and high-fat snacks) could improve GV. If both the high-protein and high-fat snacks show significant improvement effects, we will further directly compare the high-protein snack (combining milk powder and soy powder into one group) with the high-fat snack (almonds) interventions to evaluate which is better. Third, we will also compare the milk powder group with the control group and the soy powder group with the control group, and if both high-protein snack groups show significant improvement, we will further compare the animal protein and plant protein groups directly to verify whether the plant protein group is similar to the animal protein group. Finally, we will compare all the results from different dietary patterns to determine whether premeal snacks have similar effects under habitual diet and standard balanced meals.

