### Statistical methods

#### Sample size determination

The mean amplitude of glycemic excursions (MAGE) was chosen as the primary outcome indicator and it is expected that the MAGE will be reduced by 20% based on a study by Imai (33). Using PASS software (version 11.0), a sample size of 6 participants per group is required using the non-inferiority test for comparison of sample means. Assuming a 20% dropout rate, the sample size required for this study is 8 participants for each group.

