#### Statistical analysis plan

All parameters will be assessed for normality using the Kolmogorov-Smirnov test, and homogeneity of variance will be tested using the Levene test. Descriptive statistics will be expressed as the mean ± standard deviation (SD) for normally distributed data and as the median (Q1-Q3) for non-normally distributed data. Mean changes in parameters within the group will be assessed by calculating the difference between pre and postintervention measurements. When the data are normal and the variance is equal, paired *t*-tests will be used to assess the effect of interventions. Differences between groups will be assessed using the variance ANOVA test. Dunnett's test will be used to determine whether there is a significant difference between the experimental and control groups. When the assumptions for parametric tests are not met in the data, non-parametric statistical methods will be used.

Subgroup analyses by sex will be performed to explore whether the effect is modified by sex. The correlations between physiological factors and blood glucose levels will be assessed by Pearson's or Spearman's correlation analysis. Some *post-hoc* exploratory analyses will also be conducted. All analyses will be performed using SPSS version 24.0 (SPSS Inc. Chicago, IL, USA). The criterion for statistical significance will be a two-tailed *p* < 0.05.

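### MAGE is named as the primary outcome and used for sizing, but TIR, AUC, CV and MODD are also primary, in two periods, and Dunnett's test covers only part of the resulting testing

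*Protocol article*

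**What the plan says.** Under Primary outcomes, the article first names one outcome: "The change in the MAGE before and after the intervention was chosen as the primary outcome for several reasons". The same paragraph ends by adding TIR, AUC, CV "and mean of daily differences (MODD), are also included in the primary outcomes". The added indicators are introduced as examples, so the list is open and holds at least five outcomes.

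Under Sample size determination there is again only one: "The mean amplitude of glycemic excursions (MAGE) was chosen as the primary outcome indicator".

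The Continuous glucose monitoring section gives each period its own starting point: "data from D2 and D9 will be used as baseline values of two intervention periods". Neither period is named as the decisive one.

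The Comparisons section begins with a pooled test, in which "the three intervention arms will be combined as a group and compared with the control group". It then lists four further comparisons with control: the two protein arms pooled, almonds, milk powder and soy powder. None of these five is conditional. Two direct comparisons (protein versus fat, animal versus plant protein) follow only if both of their components show significant improvement over control.

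The Statistical analysis plan section names Dunnett's test for experimental against control groups, and closes: "The criterion for statistical significance will be a two-tailed *p* < 0.05".

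**The concern.** One primary outcome and an open list of at least five cannot both be the plan. The difference matters because the list is repeated over two periods and several comparisons, and no stated rule says which result decides the trial.

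Two things are at stake. First, a false-positive primary finding becomes several times more frequent than 5%. Second, the article's own gates lose their meaning. The direct comparisons open on significant improvement, but the text does not say on which indicator or in which period. Whichever indicator happens to be significant could open the step that leads to the soy-versus-milk question.

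**Working it through.** **Inputs from the article.** At least 5 primary indicators (Primary outcomes). 2 periods (Continuous glucose monitoring). 5 unconditional comparisons with control (Comparisons). Two-sided 0.05, with Dunnett for experimental versus control groups (Statistical analysis plan). 4 arms of 8.

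**The plan's own figure.** 6 / (1 − 0.20) = 7.5, rounded up to 8 per arm; 4 × 8 = 32. The dropout step reproduces. No familywise error rate is stated, so there is none to reproduce.

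**Counting the tests.**
- All snacks versus control: 5 indicators × 2 periods = 10 p-values.
- All five comparisons: 10 × 5 = 50. Of these, 3 × 10 = 30 are single-arm tests, forming 10 separate Dunnett families of three. The other 2 × 10 = 20 are pooled contrasts, outside Dunnett.

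**Bound for independent tests,** 1 − 0.95^k:
- k = 5: 22.6%
- k = 10: 40.1%

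**Simulation for correlated tests.** The article gives no correlations, so they are assumed: 0 to 0.9 between indicators and 0 to 0.8 between periods. No snack has any effect, n = 8 per arm, pooled-variance two-sided t tests, 20,000 runs, simulated Dunnett critical value 2.48. The entries are the chance of at least one significant result in either direction. Columns give the correlation between indicators / between periods.

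| Tests counted | 0 / 0 | 0.5 / 0.5 | 0.9 / 0.8 |
|---|---|---|---|
| All snacks vs control, 10 tests | 40% | 32% | 16% |
| Dunnett on the three single arms only | 40% | 33% | 17% |
| Dunnett on single arms + two pooled contrasts at 0.05 | 56% | 46% | 24% |
| All five comparisons at 0.05, no Dunnett | 75% | 64% | 35% |

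A separate run of 6,000 gave 41% and 57% where this one gives 40% and 56%, which is within simulation error. Results with 6 per arm are almost the same. The third row is the closest to the plan as written.

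**Does naming MAGE alone suffice?** No. With both periods kept, Dunnett on the single arms and the two pooled contrasts at 0.05, the chance is still about 13–16% (a repeat run put the low end nearer 12%). With all five comparisons unadjusted it is 20–25%.

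**The case against.** **Dunnett is in the plan.** A reader might infer that every comparison is tested separately at 0.05, and so quote the last row of the table (35–75%). The article does not support that: almonds, milk and soy against control are exactly the family that Dunnett's test protects. This objection stands, and the figures used here credit Dunnett.

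**The overall claim has its own test.** A reader might infer that a general benefit of premeal snacks could be claimed from any of dozens of p-values. The Comparisons section ties that claim to the first, pooled comparison, which gives about 10. The other contrasts answer narrower questions, and the direct ones are conditional. This also stands, which is why the 10-test figure is given separately.

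**The indicators are related.** All five come from the same glucose trace, so high correlation is plausible and the low end of each range may be nearer the truth. That is fair, but even there the risk is about three times nominal (16%) or about five times (24%).

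**The two periods answer different questions.** Habitual and standard diets are separate stated aims. That is so, but it does not settle which of them decides the trial. The sentence "We will assess changes in these outcomes in two different experimental periods" is weak support for the two-period count, because it stands under Secondary outcomes. The separate D2 and D9 baselines, and the closing comparison of diet patterns, are the better evidence.

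**An unseen analysis plan may hold the adjustment.** Absent detail alone would be no finding. What remains is on the page: the primary outcome is stated in two incompatible ways, and the listed comparisons are attached to a single 0.05 criterion.

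**Conclusion.** The point holds in this form: the article contradicts itself on whether it has one primary outcome or at least five, names no primary period, and states error control for only part of the testing. Against a nominal 5%, the chance of at least one false-positive primary result is about 16–41% for all snacks versus control, and about 24–57% with Dunnett on the single arms plus the two pooled contrasts.

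The ranges assume no effect of any snack, 8 completers per arm, exactly five indicators and the correlations given above. They count differences in either direction, so a false claim of benefit alone would be less frequent.

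A reader might go further and call a false-positive result likely. With Dunnett counted, the chance passes one half only when correlations are low, so the article supports a materially inflated risk and no more than that.

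**What to change.** 1. Make change in MAGE the sole primary outcome, in one period named in advance. The first is a reasonable choice because its baseline (D2) precedes any snack exposure; D9 follows the snacks of the first period. The choice is the sponsor's.
2. Make all snacks versus control the primary test, at two-sided 0.05.
3. Test the other MAGE contrasts in the article's own order. Pooled protein and almonds versus control (Holm) follow only if the first test is significant. Soy and milk versus control (Holm) follow only if both second-step contrasts are significant. Without that full gate the familywise rate is not assured. Say that this order takes the place of Dunnett for these contrasts.
4. Move TIR, AUC, CV, MODD and the other period to secondary.
5. State that the significant-improvement conditions for the direct comparisons refer to MAGE in the named period.
6. State where the soy-versus-milk non-inferiority hypothesis sits in this order. The sample size was derived from a non-inferiority test, so this is a decision for the sponsor and not only an edit.

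If all five indicators had to stay primary in both periods, Bonferroni would leave 0.05 / 10 = 0.005 per test, before counting comparisons.

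The text changes are confined to the outcomes, comparisons and analysis sections, with no new data. The real cost is that the other glycemic indicators and one diet period lose primary status, although the two-diet comparison is a stated aim.

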#### Secondary outcomes

Secondary outcomes consist of various metabolic and behavioral indicators, including changes in insulin, C-peptide, fasting blood glucose (FBG), HOMA-IR, HOMA-β, subjective appetite, satiety, hunger evaluated by the VAS, body height, and weight measurements.

We will assess changes in these outcomes in two different experimental periods: [1] from baseline to the end of the first intervention period (D3-D6) and [2] from the end of the run-in period to the end of the second intervention period (D10-D13). The acceptability and maintainability of the intervention will also be assessed after the completion of the interventions (D14).

### Outcome measures

#### Test days

All clinical examinations will be carried out at Wenzhou Medical University. Participants will arrive at The 2nd Affiliated Hospital and Yuying Children's Hospital of WMU at 8:00 am after 12 h of overnight fasting (V1). All subjects will be asked to eat the same dinner between 17:00 and 19:00 the day before the experiment to minimize the potential effect of different dinners on fasting blood glucose and insulin levels of the next day (31). In addition, no alcohol consumption or strenuous physical activity will be allowed during the 72 h before the experiment.

#### Continuous glucose monitoring

A 2-week CGM system (FreeStyle Libre Flash Glucose Monitoring System, Abbott) will be initiated on the test day at V1. The CGM will be attached to the hypogastrium on the test day morning. Subjects will be asked to measure their blood glucose levels using a glucometer (glucometer 550, Yuwell) four times a day (before breakfast, lunch, dinner, and bedtime) during the CGM measurement period to calibrate the instruments. The CGM will monitor dynamic blood glucose within the next 15 days. To exclude the potential impact of confounders, the data of dynamic blood glucose from D1, D3, D10, and D14 will be excluded in the final analysis, while data from D2 and D9 will be used as baseline values of two intervention periods. We will only use the data from the latter 3 days of each period rigorously and conservatively to maximally control the potential data contamination.

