### Intervention

This study consists of a baseline blood glucose assessment day (D2) under habitual diet conditions (before the start of the intervention, V1), two intervention periods under two different diet patterns with equal experimental days (D3-D6, D10-D13), and a standard balanced meal run-in period between the two intervention periods (D7-D9). A 3-day experiment run-in period will be set before Visit 1 (V1). During this period, all subjects will be asked to maintain their habitual eating without energy restrictions and maintain a regular daily schedule. In addition, they will not be allowed to smoke, drink, or perform vigorous exercise in the course of this trial. All subjects will wear continuous glucose monitoring (CGM) to monitor dynamic interstitial glucose in the mornings of V1. The first intervention period will be under the habitual diet condition from D3 to D6 (4 days), during which all subjects will be asked to maintain their habitual eating and daily activities, similar to the experimental run-in period. After the first intervention period, a 3-day standard balanced meal run-in period from D7 to D9 will be performed before the second intervention to ensure that the standard meals are tolerable to the individual participants. The second intervention will consist of prelunch snacks with standard meals that had the same macronutrient composition as those in the run-in period. Screening will be finished within 1 week before the experiment (V0). Randomization will be performed after the completion of screening. Outcomes will be assessed after the two intervention periods. Blood samples will be taken before and after the two intervention periods (V1-V4), and interstitial glucose will be monitored throughout the 2 week experimental period. An overview of the study visits is presented in Table 2. During the entire period of this experiment, subjects will be asked to complete a food recording diary (online) including the type, amount, and time of all meals, snacks, and drinks except water (in the form of photos and text). Subjects will be supervised daily by the researcher in charge to ensure their food diaries are uploaded on time. Physical activity and sleep will also be recorded via a mobile app for step count and sleep time records.

**Table 2 T2:** Overview of study visits.

**Visit**	**V0**	**V1**	**V2**	**V3**	**V4**
Time from the start of wearing CGM^a^	−7	1	7	10	14

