Another important advantage of the trial is that we will implement a premeal snack intervention under two different dietary conditions. Several studies have reported the beneficial effects of premeal snack interventions on glucose metabolism under well-controlled dietary patterns (14, 40, 42). Although the effects observed in this way are significant, such studies under well-controlled conditions could not represent the full extent of this benefit in real daily diet because GV itself can vary with the order of meals, macronutrient ratios, and the interval between meals (11). The purpose of this design is to determine whether the intervention, when applied to a daily diet, will result in improvements similar to those obtained under the experimental control diet. First, before the start of the experiment, we will set a run-in period with the aim of testing the baseline GV levels of the subjects as their own control. After the run-in period, the first period of the intervention will begin, and premeal snacks will be given under exactly the same habitual diet conditions as those in the run-in period, during which no restrictions will be imposed on the amount and type of food consumed by the subjects at their regular meals. After the end of the first intervention period, a standard balanced meal run-in period will be set to ensure that the subjects' metabolism adapts to this meal pattern before the start of the second intervention period, to obtain more stable data for the second-period results.

Notably, as the prediabetic population continues to expand, the solution to reduce the risk of the development of diabetes in this population is an urgent issue. It has been reported that in the process of disorders in glucose metabolism, the increase in postprandial glucose excursion and delayed duration of postprandial glucose excursion occurs earlier than the increase in FBG levels in patients with prediabetes (43). Our study will select subjects from the pre-diabetic population aim to alleviate glucose metabolism and achieve prevention through simple and easily implemented lifestyle interventions. In addition, the results from the prediabetic population are more likely to be extrapolated to diabetic populations.

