Furthermore, we will control for confounding factors as strictly as possible. This protocol is based on past studies of the effects of different intervention time points, intervention foods, intervention energies, and intervention populations. However, this study is extended by physical activity level monitoring and daily nutritional recordings (electronic food diary, CGM, and activity records) through timely supervision of the subjects by the researchers and hunger, satiety, and blood glucose and insulin resistance indices will be measured before and after energy intake. During both the ad libitum and standard meal periods, subjects will be asked to record whether and how much food is left over from each meal to assess the effect of the intervention on energy intake at regular meals and to exclude changes in GV due to differences in energy intake. To exclude the influences of different dietary patterns, researchers will train the subjects to eat in the same fixed meal order and have the same duration of each meal (chewing pace) to control for confounding factors in the 3-day balanced meal run-in period. At the end of the experiment, subjects will also be surveyed about their perceptions of the intervention to obtain information about its acceptability, compliance, and adherence. Compared to previous studies, these tools and measures will help avoid confounding factors, advance the understanding of the effect of the premeal snacking intervention on GV and promote the application of the intervention to a wide range of the population. Moreover, we will also administer 250 ml of water to the control group, similar to the 3 intervention groups, to avoid the influences of stomach capacity and swallowing behavior changes on the results (44, 45). In addition, for data processing, we will exclude data from the first day of each phase and the last day of wearing the CGM to exclude data differences caused by the instability of CGM devices.

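### Change in MODD, a listed primary outcome, is undefined in both periods because each baseline is a single CGM day

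*Protocol article*

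**What the plan says.** All places are in the protocol article.

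- *Primary outcomes*: change in MAGE is the lead outcome. TIR, AUC, CV and "mean of daily differences (MODD), are also included in the primary outcomes".
- *Statistical analysis plan*: within-group effects on parameters are differences between measurements before and after the intervention, tested by paired t-test where assumptions allow. Arms are compared by ANOVA and Dunnett's test.
- *Continuous glucose monitoring*: "the data of dynamic blood glucose from D1, D3, D10, and D14 will be excluded in the final analysis". Of the rest, "data from D2 and D9 will be used as baseline values of two intervention periods". On the intervention side, "We will only use the data from the latter 3 days of each period".
- *Intervention*: the first baseline is confirmed as "a baseline blood glucose assessment day (D2) under habitual diet conditions". Snacks are given on D3-D6 and D10-D13. D7-D9 is a run-in on standard meals, which the section on that run-in describes as snack-free. The sensor is fitted on the morning of V1, after the initial 3-day run-in.
- *Discussion*: "we will set a run-in period with the aim of testing the baseline GV levels of the subjects as their own control"; and, on data handling, "we will exclude data from the first day of each phase and the last day of wearing the CGM".

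**The concern.** MODD is by construction a between-day measure: the mean absolute difference between readings at the same clock time on consecutive days. A window of one day contains no such difference. The article fixes one-day baselines and also fixes a pre/post analysis for parameters in general, and for MODD these two instructions cannot both be followed.

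If this stays open, the handling of a listed primary outcome will have to be improvised once the data are in. A related question arises for the other indices. Each is compared between a one-day and a three-day window, and the article does not say whether three days are averaged day by day or pooled. Pooling brings between-day variation into the later value that the earlier value cannot contain, so a within-group paired test could register a difference caused only by window length.

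**Working it through.** **1. Day count.** The inputs are the exclusions, baselines and day ranges given in *Continuous glucose monitoring* and *Intervention*. Day-pairs are consecutive days lying inside the same window.

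| Window | Days | Number of days | MODD day-pairs |
|---|---|---|---|
| Period 1 baseline | D2 | 1 | 0 |
| Period 1 post | D4, D5, D6 | 3 | 2 |
| Period 2 baseline | D9 | 1 | 0 |
| Period 2 post | D11, D12, D13 | 3 | 2 |

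The article's three analysed days per period reproduce: four intervention days less D3, and four less D10. Of D1 to D14, only D7 and D8 are neither excluded nor given a use.

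**2. Can a neighbouring day supply a baseline pair?** In period 1, no: D1 and D3 are both excluded, and D3 is also a snack day. In period 2, D8 adjoins D9 and is not excluded, but the article does not assign it to the baseline. As written, change in MODD is undefined in both periods.

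**3. Unequal windows, daily values averaged.** Let s² be a person's day-to-day variance of a daily index, with independent days, b baseline days and p post days.

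Variance of change = s² × (1/b + 1/p)

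- b = 1, p = 3: 1 + 0.333 = 1.333 s². The single baseline day contributes 1/1.333 = 75%.
- b = 2, p = 3: 0.500 + 0.333 = 0.833 s². The reduction is 1 − 0.833/1.333 = 37.5%.

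Averaging daily values introduces no expected bias from window length; the cost of one baseline day is precision.

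**4. Unequal windows, readings pooled.** Let v be the variance of daily means as a fraction of within-day variance. With no intervention effect, expected 3-day variance / expected 1-day variance = 1 + v × 2/3.

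The article gives no value for v. Assuming 0.05 to 0.20:

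- v = 0.05: 1.033, or √1.033 = 1.016 on the SD scale
- v = 0.20: 1.133, or √1.133 = 1.065 on the SD scale

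This is 3% to 13% in variance and about 1.6% to 6.5% in SD or CV. A simulation with other assumed inputs (mean 6.0 mmol/L, one-day CV about 10.8%, SD of daily means 0.2, 0.4 or 0.6 mmol/L) gave pooled 3-day CVs higher by about 0.4, 1.3 and 2.6 CV points with no treatment effect. These figures are illustrations only. The shift is expected in every arm alike, so it bears mainly on within-group tests.

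**5. Where D8 stands.** Dropping the first day of each phase, as the Discussion describes, removes D7 from the D7-D9 run-in and leaves D8 and D9. Using both gives two baseline days and 1 MODD pair in period 2. Period 1 is unchanged, with 0 pairs.

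**6. The Discussion sentence on the run-in.** It presents the initial run-in as the measurement of baseline glycemic variability, but the sensor is fitted at V1, after that run-in. The only CGM baseline on the habitual diet is D2.

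**The case against.** The defence is right on several points.

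- A reader might infer that MODD cannot be produced at all. The documents do not support that. *Primary outcomes* attaches the word change explicitly only to MAGE, and MODD over D4-D6 and D11-D13 exists and can go straight into the planned ANOVA and Dunnett comparisons. Only the change score and the paired test are lost.
- A reader might infer that the unequal windows bias the main results. The article does not say that readings are pooled, and such a computational detail may sit in a fuller document. Daily averaging leaves no expected bias. Pooling would move all four arms together and so would mostly spare the between-arm contrasts. TIR, as a percentage, has no systematic dependence on window length either way.
- A reader might infer that D8 is wrongly thrown away. The article never lists it as excluded. The Discussion says the standard-meal run-in lets metabolism adapt to the new meals, which is a coherent reason to prefer D9, and the first-day rule does not oblige anyone to use every remaining day as baseline. The 37.5% gain also requires D8 and D9 to be exchangeable, which an adaptation phase puts in doubt.

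The contradiction over MODD survives all of this: the article itself states the one-day baselines, the primary status of MODD and the general pre/post method.

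**Conclusion.** The point holds for MODD. With 0 baseline day-pairs in each period, its change score does not exist under the plan as written. This rests only on the article's own day list and on the definition of MODD.

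It should be fixed, but it does not undermine the trial. MODD is one of five listed indices and is not the one used for the sample size, MAGE can be calculated in all four windows, and the repair uses data already being collected.

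The window-length issue is conditional: it becomes a bias only if readings are pooled, its size rests on assumed variance ratios, and it would chiefly touch the within-group paired tests. The D8 option is a possible gain in precision, not the correction of an error. The Discussion sentence about the run-in is a slip of wording that changes no analysis, since *Intervention* and *Continuous glucose monitoring* both name D2.

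**What to change.** 1. State that MODD is analysed as a post-intervention comparison between arms, over D4-D6 in period 1 and D11-D13 in period 2, with no change score and no paired test. Cost: no within-person reference for MODD, so chance differences between arms of 8 stay unadjusted.
2. State that MAGE, CV, AUC and TIR are computed for each 24-hour day and averaged over the days of the window. Cost: one sentence.
3. Correct the Discussion to say that baseline variability on the habitual diet comes from D2.
4. Optional: define the period 2 baseline as the mean of D8 and D9. This brings the precision gain shown above, if the two days are exchangeable, and one baseline MODD pair. The cost is a two-day baseline in one diet period and a one-day baseline in the other, although *Comparisons* plans to set the two diets side by side. If that comparison matters more than precision within period 2, keep D9 alone and give adaptation as the reason.

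All of this is analysis wording. Settle it while the analysts are still blinded to allocation, as *Randomization and allocation concealment* provides.
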